#### Secondary outcome measures

These will include outcomes such as MPR, Morisky Medication Adherence Scale (MMAS) score and Competence and Autonomous Self-regulation Scale scores.

Table 1 shows all outcome variables, questionnaires to be used and when they will be administered. We will assess self determination theory-related constructs of competence [48, 49], and autonomous self-regulation [50, 51]. We will also assess HTN knowledge [52, 53], medication side effects, stroke knowledge, self-reported medication adherence (MMAS), beliefs and life goals [54, 55] and MPR [56].

### Participant timeline

Algorithms for participant recruitment and follow-up assessments are shown in Fig. 1.

#### Proposed sample size

For this feasibility cluster RCT we will recruit 15 patients per cluster (i.e., physician), 30 patients per group (intervention versus control group) (total *n* = 60). We agree with Kraemer et al. [57] that pilot feasibility studies are deficient in estimating effect size with sufficient accuracy for future study design. To this end we will evaluate the availability of subjects, assess proportions approached/consented, and examine the feasibility of PINGS by evaluating adherence and retention rates. Thus, sample size justification focuses on the precision of estimates rather than the power of statistical tests. We will recruit 30 subjects (15 per physician = cluster) per treatment group based on number of degrees of freedom within each cluster, as suggested by Mead, to obtain reasonable precision for variance estimates [58].

#### Recruitment

A list of eligible patients will be identified from hospital medical records by a research assistant (RA) with the identity of the patients’ doctors not included. The research coordinator (RC) will contact and schedule eligible patients for screening/recruitment and obtain informed consent voluntarily from patients who are interested in the study. Subjects whose SBP averages ≥140 mmHg from the last two readings of the 10-min protocol will have their height, weight and waist circumference measured. A set of questionnaires will be administered to assess study outcome measures (see Table 1). The study site admits an average of 43 stroke patients each month. Based upon the stroke with HTN incidence patterns in the KATH and SMASH pilot work [38–40, 47], we will recruit eight patients (four intervention group patients and four control group patients) per month for enrollment into the study.

#### Allocation and concealment

Randomization of subjects in blocks of four will be conducted by a statistician using a computer-generated random sequence of numbers. Participants who consent to the study will be allocated to either of the two intervention clusters or the two control clusters at the baseline visit using the computer-generated randomization sequence. Each sequence generated will be kept concealed in an envelope which will be opened by the research coordinator in the presence of the consenting eligible study participant at enrollment.

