## Methods

### Trial design

This is a two-arm cluster randomized controlled trial involving 60 stroke survivors with the physician as unit of randomization and patients as unit of analysis. Each of the four physicians will be recruited and randomly assigned to the intervention or control group by the statistician (who is not involved in provider or patient recruitment nor data collection) using a computer-generated random sequence. Four groups/clusters of 15 eligible patients will be assigned to either control or intervention arms by the study coordinator after having met study criteria for enrollment (Fig. 1). A cluster randomized trial has been chosen to avoid potential treatment contamination in which physicians might unintentionally provide patients with different degrees of attention or blending of treatment protocols. The checklist for the study protocol is provided as Additional file 1.

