### Control arm/standard of care

Inclusion criteria include owning a cell phone with at least SMS and voice mail. To control for attention exposure, they will receive SMS messages dealing with healthy lifestyle behaviors (smoking, diet, physical activity) but not with medication adherence, hypertension- or stroke-related issues. Messages will be of the same frequency and size as those in the intervention arm. Every 3 days (comparable to those in the intervention arm) they will receive lifestyle messages and if they have a smartphone, the SMS messages will have either PDFs attached or weblinks to a brief video clip or series of charts, information, and so forth. This information will be sent in two messages and requires 3–5 min per message to view or listen to (similar to the BP protocol duration). All four physicians will receive the expert consensus guideline charts. Intervention tactics will cease for both groups after the 3-month trial.

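### The protocol never settles whether physicians or patients are randomised, and the coordinator who enrols patients also opens the envelopes under a fixed block of four

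*Protocol article*

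**What the plan says.** The protocol article describes allocation in several places.

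- **Trial design, unit.** The trial is cluster randomised "with the physician as unit of randomization and patients as unit of analysis".
- **Trial design, physicians.** "Each of the four physicians will be recruited and randomly assigned to the intervention or control group by the statistician". The statistician takes no part in recruitment or data collection.
- **Trial design, next sentence.** Four groups of 15 eligible patients "will be assigned to either control or intervention arms by the study coordinator after having met study criteria for enrollment". The reason given for clustering is to avoid contamination between arms.
- **Abstract, Methods.** Patients are randomly allocated by a computer sequence into four clusters of 15, one cluster per physician and two clusters per arm.
- **Allocation and concealment.** "Randomization of subjects in blocks of four will be conducted by a statistician", and then: "Participants who consent to the study will be allocated to either of the two intervention clusters or the two control clusters at the baseline visit". The sequence is held in an envelope, "opened by the research coordinator in the presence of the consenting eligible study participant at enrollment".
- **Recruitment.** The research coordinator contacts, schedules and consents patients. The list of eligible patients is drawn up without their doctors' identities. Planned accrual is eight patients a month, four per arm.
- **Statistical analyses, Primary outcome measures.** The mixed model allows for clustering within physician, and an intracluster correlation coefficient (ICC) will be estimated to size a future trial.
- **Phone requirement.** Inclusion criteria accept a phone owned by the patient or by a relative in the same home. The Control arm section says: "Inclusion criteria include owning a cell phone with at least SMS and voice mail".

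**The concern.** Randomising four physicians who bring their own patients is a cluster trial in which patients are recruited after the clusters have been allocated. Randomising individual patients to physicians whose arm is already fixed is an individually randomised trial with clustering by provider. The two differ in their risk of selection bias and in what the between-physician variance means. The article uses the language of both. A third statement, that the coordinator assigns groups to arms, fits neither cleanly.

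Concealment is a second matter. One role recruits, consents and opens envelopes, so it sees every earlier allocation at a single site, and the block size is printed in the protocol. Someone who can anticipate the next allocation can, knowingly or not, influence who is approached or when. With 60 patients and four physicians, such selection would not average out, and BP control is compared between arms as a primary outcome.

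**Working it through.** **1. Structure of the sample.** From Proposed sample size: 4 physicians × 15 patients = 60, and 2 × 15 = 30 per arm. From the block size: 60 / 4 = 15 complete blocks. The numbers agree, so the problem is not in the sample size. The article gives no power calculation to reproduce; the size is justified by precision.

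**2. The statements side by side.**

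| Place | What is randomised or assigned | By whom |
|---|---|---|
| Trial design, physicians | 4 physicians to arms | Statistician |
| Trial design, next sentence | 4 groups of 15 patients to arms | Study coordinator |
| Abstract; Allocation and concealment | Individual patients to clusters, in blocks of four (the block size is given only in the latter) | Statistician's sequence; envelope opened by research coordinator |

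- *Physicians only.* The text on allocating patients is then wrong. With two physicians per arm there are only C(4,2) = 6 possible allocations.
- *Patients only.* The physician as unit of randomisation is then wrong.
- *Two stages.* The first and third rows fit together. The physician as sole unit of randomisation is still wrong, and so is the second row, because each group's arm was fixed when its physician was randomised.

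Every reading requires some text to be corrected.

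**3. Meaning of the ICC.** If patients stay with their own doctors, variation between physicians combines practice effects with systematic differences in patient mix. If patients are randomised to physicians, mix differs only by chance. The ICC carried into a future trial is therefore a different quantity under each scheme.

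**4. Predictability with a fixed block of four.** Assumptions: blocks are 2:2 by arm, and the observer knows the block size and all earlier allocations. The six possible orders (I = intervention, C = control) are:

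- IICC and CCII: the 3rd and 4th positions are determined, so 2 each.
- ICIC, ICCI, CIIC and CICI: only the 4th position is determined, so 1 each.

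Determined positions: (2 × 2) + (4 × 1) = 8 out of 6 × 4 = 24, which is 1/3. Over the trial, 60 × 1/3 = 20 allocations are certain in advance.

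The chance of a correct best guess, by position, is:

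- 1st: 1/2.
- 2nd: 2/3.
- 3rd: (1/3 × 1) + (2/3 × 1/2) = 2/3.
- 4th: 1.

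The mean is (1/2 + 2/3 + 2/3 + 1) / 4 = 17/24 = 70.8%, or 42.5 of 60, against 30 of 60 by chance. Blocks holding one patient for each of the four physicians give the same 1/3 and 17/24 at arm level.

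**5. If allocation follows the treating physician.** Once physicians have been randomised, a patient's arm is known as soon as the doctor is known. The upper bound is 60 of 60. It requires the coordinator to know both the physicians' arms and each patient's doctor.

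**The case against.** The strongest reply is that the text can be read as one two-stage scheme. The Allocation and concealment section speaks of intervention clusters and control clusters as already existing, and Trial design says how they came about. The coordinator's assignment of groups could be a loose description of opening the envelopes, since both follow eligibility. The mixed model already allows for clustering within physician, so the analysis need not change. This is a fair reading, and it rules out the inference that the trial could not be run. It does not remove the point: the article never states the two stages, and under them its own design label is wrong.

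A reader might also infer that the coordinator can foresee allocations as a matter of fact. The article does not support that. It says that the sequence is concealed, that allocation follows consent, that the statistician is separate from recruitment, and that doctors are left off the eligibility list. It gives neither the composition of the blocks nor the coordinator's knowledge of their size. What stands is the weakness of combining a fixed, published block size with one role that enrols and opens every envelope. Omitting the doctor from a list does not prevent the coordinator from learning it in another way.

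A third tempting inference is that eligibility differs by arm because the phone wording in the control section is narrower and intervention patients may be lent a phone. That section does not limit the criterion to controls, eligibility is settled before allocation, and the loan supplies equipment and is not an entry rule. Only a mismatch in wording remains.

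Finally, this is a feasibility pilot that is not sized for power. That limits the consequences, but the arms are still compared on BP control and the ICC is meant for later use.

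**Conclusion.** The point holds as an inconsistency in the stated unit of randomisation together with an avoidable weakness in concealment. The inconsistency rests on the text alone and needs no assumption. It is a conflict between statements, not a detail that a condensed article leaves to a fuller document.

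The size of the concealment problem is conditional. It is 20 of 60 allocations certain in advance if blocks are 2:2 by arm and the coordinator knows the block size and past allocations. It is up to 60 of 60 only if patients stay with their own doctors and the coordinator learns who they are. Both figures treat the study coordinator and the research coordinator as one role. Planned accrual of four per arm per month is compatible with 2:2 blocks but does not establish them. The phone wording is a minor edit.

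**What to change.** Before recruitment, amend the protocol as follows.

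1. State one scheme and say how patients reach physicians, including whether a patient may be moved from an existing doctor. If it is two-stage, describe it as individual randomisation with clustering by physician, and interpret the ICC accordingly.
2. Delete the assignment of groups to arms by the study coordinator.
3. Use randomly varying block sizes that are not disclosed to recruiting staff.
4. Release each allocation only after eligibility and consent are recorded, through a person or system separate from the enrolling coordinator. This could be the statistician centrally, or REDCap if its randomisation function is available; the article mentions REDCap only for data entry.
5. Align the phone wording in the Control arm section with the Inclusion criteria, so that one criterion applies to every patient before allocation.

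The cost is a short amendment, minor set-up work and slight short-term imbalance between arms from varying blocks. Sample size and analysis model can stay as they are.

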#### Blinding

Physicians who will be assessing primary outcomes and research assistants assessing feasibility and secondary outcomes will remain blinded as to the patients’ group status throughout study (i.e., preintervention, 3-, 6- and 9-month evaluations).

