**Methods:**

This two-arm cluster randomized controlled feasibility pilot trial will involve 60 recent-stroke survivors. Using a computer-generated sequence, patients will be randomly allocated into four clusters of 15 patients each per physician: two clusters in the intervention arm and two in the control arm. Patients in the intervention arm will receive a simple pillbox, a Blue-toothed UA-767Plus BT BP device and smartphone for monitoring and reporting BP measurements and medication intake under nurse guidance for 3 months. Tailored motivational text messages will be delivered based upon levels of adherence to the medication intake. Both groups will be followed up for 6 months to compare BP control at months 3, 6 and 9 as primary outcome measure. Physicians assessing BP control will be blinded to arms into which patients are allocated. Secondary outcome measures will include medication adherence scores and Competence and Autonomous Self-regulation Scale scores. A qualitative study is planned after follow-up to explore the lived experiences of participants in the intervention arm.

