#### Provider level

Physicians in the intervention arm will receive summary reports of their patients’ adherence to their medications and BP data tailored by them (e.g., average and range of SBP/DBP readings, percent of SBP/DBP controlled, and so forth) every 2 weeks using only patient ID numbers. They will also receive summary charts of expert consensus BP management guidelines used in other studies [47]. If a patient’s mean BP exceeds the thresholds, the PINGS nurse navigator will call the patient and conduct the BP protocol again, and initiate a follow-up action as needed. The nurse navigator will also contact those patients who show medication adherence below .80 and/or whose monthly MPRs do not reflect the information in the self-reported medication intake summary reports. They will use motivational interviewing to help the patient to eliminate the barriers related to poor medical regimen adherence.

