### Follow-up phase

Subjects in both arms of the study will be followed up for 6 months after the initial 3-month trial. During the follow-up period, subjects will attend clinics monthly where their physicians will assess them clinically. At months 3, 6 and 9 post enrollment patients and providers will undergo assessments on methodological parameters and consumer responses, clinic BP measurements, medication adherence, health literacy on stroke and HTN as well as self-determination theory constructs such as Autonomous Self-regulation and Competence Scales. Physicians in both groups will also undergo assessment on adherence to BP management protocols (Fig. 1 and Table 1).

**Table 1 Tab1:** Study outcome measures

Outcomes	Psychometrics (internal consistency [α], test-retest reliability [r]) NOTE A^a^	Time points
Primary outcomes		
Feasibility: methodological parameters and consumer responses	Recruitment and retention rates; Self-report: Patient/Provider Satisfaction Scale (.82–.96, test-retest (1 week) .98) [74, 75], fidelity checklists: patient level (e.g., connection; BP uploads via phone; opening of messages/educational information and provider level (e.g., delivery of provider summaries; phone alerts)	Baseline, 3, 6, 9 months
Clinic: BP	Clinic-based BP	
Feedback and refinement	Focus groups	Providers and IG: 9 months
Secondary outcomes		
Medication adherence Physician adherence	Medication Possession Ratio (MPR); Morisky Medication Adherence Scale (α = .76–.83, r = .64) [76, 77], provider guideline adherence: timely med changes (date of script changes following BP feedback (bi-monthly PINGS reports/clinic BPs)	Baseline, 3, 6, 9 months
Self-determination theory constructs	Autonomous Self-Regulation (α = .81–.84, r = .38) [78], Competence Scale (α = .88–.95, r = .32–.46) [51, 52, 78].	
Potential moderators/mediators		
Demographics	Age, education level, income	Baseline
HTN/stroke knowledge, health literacy, anthropometrics	Self-report: HTN/stroke knowledge (.70) [54, 55], health literacy (r = .74, .82) [78–80], Height/ weight/girth	Baseline, 3, 6, 9 months
Medication adherence factors	Side effects, adverse events	As reported, and 3, 6, 9 months

^a^Basic psychometric property analyses (e.g., internal consistency, test-retest reliability) will be conducted during first 3 months on scales, which have not been used with Ghanaian stroke patients

*BP* blood pressure, *HTN* hypertension, *IG* Intervention Group

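### The physicians said to assess BP blind are, as far as the protocol describes, the four randomised cluster physicians, who would know their patients' arm; independent assessors must be named or the blinding claim withdrawn

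*Protocol article*

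**What the plan says.** The Blinding section says: "Physicians who will be assessing primary outcomes and research assistants assessing feasibility and secondary outcomes will remain blinded", and applies this to the preintervention, 3-, 6- and 9-month evaluations. The abstract says: "Physicians assessing BP control will be blinded to arms into which patients are allocated".

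The Trial design section describes a cluster trial "with the physician as unit of randomization and patients as unit of analysis" and adds: "Each of the four physicians will be recruited and randomly assigned to the intervention or control group by the statistician". The abstract gives the cluster structure: "patients will be randomly allocated into four clusters of 15 patients each per physician: two clusters in the intervention arm and two in the control".

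Under The intervention, Provider level: "Physicians in the intervention arm will receive summary reports". These cover their own patients' medication adherence and BP, are issued every 2 weeks and carry patient ID numbers only. The Control arm section gives all four physicians the guideline charts but describes no patient reports for control physicians.

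The Follow-up phase section says that "subjects will attend clinics monthly where their physicians will assess them clinically". Its next sentence lists clinic BP among the assessments at months 3, 6 and 9 without saying who measures it. BP control and change in clinic BP are the primary outcome measures.

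**The concern.** Blinded assessment is the stated safeguard for the primary outcome, but the article attributes it to physicians, and the only physicians it describes are randomised units. Two of the four also receive part of the intervention.

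Two features raise the stakes. BP control is a threshold endpoint, so small differences in how readings near 140 mmHg are taken, repeated or rounded can change a patient's classification. In addition, the physicians' own adherence to BP management guidelines is a secondary outcome, so they are not disinterested observers. If the outcome were read with knowledge of the arm while the report claimed blinding, readers would be misled about the risk of bias. The preliminary evidence meant to support a larger trial would carry that error forward.

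**Working it through.** The main check is one of consistency. No sample size, power or error rate enters it.

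**Step 1: what a cluster physician knows.**
- Trial design: four physicians, each assigned to one arm.
- Abstract: one cluster of 15 patients per physician, two clusters per arm, so 4 × 15 = 60 patients and 2 × 15 = 30 per arm.
- It follows that a physician's arm is the arm of all 15 of that physician's trial patients. No cluster mixes arms.

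**Step 2: whether the physician knows his or her own arm.**
- Provider level: intervention physicians receive two-weekly reports on their own patients, tailored by them. A physician who receives and shapes such reports knows the arm.
- Labelling reports by ID number hides names, not allocation. With one arm per cluster, receiving any report reveals the group of all 15 patients.

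**Step 3: whether other features restore blinding.**
- The Allocation and concealment section speaks of randomising subjects in blocks of four. Those subjects still go to the two intervention or the two control clusters, so the physician still reveals the arm.
- Intervention tactics stop after 3 months. What a physician has learned does not, so months 6 and 9 are no better protected than month 3.

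**Step 4: who assesses.**
- Blinding and the abstract: physicians, not identified further.
- Follow-up phase: the patients' own physicians see them at the monthly clinics; no measurer is named for months 3, 6 and 9.
- No section mentions a fifth physician or an independent BP assessor.

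Steps 1 to 3 show that the blinding statement cannot hold for the cluster physicians. Step 4 shows that no one else is described, but also that the identity of the assessors is inferred.

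**Illustration of size (all inputs assumed; the documents give none of them).** Suppose SBP is normal with SD 18 mmHg, there is no true effect, and readings in one arm are lower by d. The shift in the proportion below 140 is Φ((140 − μ + d)/18) − Φ((140 − μ)/18).

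| Assumed mean μ | d = 3 mmHg | d = 5 mmHg |
|---|---|---|
| 140 | 0.566 − 0.500 = 0.066 | 0.609 − 0.500 = 0.109 |
| 158 (one SD above) | 0.202 − 0.159 = 0.044 | 0.235 − 0.159 = 0.076 |
| 122 (one SD below) | 0.878 − 0.841 = 0.037 | 0.899 − 0.841 = 0.058 |

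With 30 patients per arm, the top row is 0.066 × 30 ≈ 2.0 and 0.109 × 30 ≈ 3.3 patients. The threshold at the mean is the most sensitive case. For comparison, the unadjusted 95 % half-width for a difference in proportions near 50 % is 1.96 × √(2 × 0.25/30) ≈ 0.25, before any allowance for clustering.

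**The case against.** The strongest reply is that the article never says the assessors are the four cluster physicians. The Blinding section does not identify them, the sentence about patients' own physicians concerns the monthly clinics, and this is a condensed article whose full protocol may name separate assessors. This stands as a limit on certainty. A reader might infer that the primary outcome is definitely read unblinded; the documents do not establish that. It does not remove the point, because the article makes a positive blinding claim that conflicts with the only physicians and clinic arrangements it describes.

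Three further inferences are tempting and should not be drawn:
- **That baseline and follow-up BP are measured by different methods.** The Blinding section includes the preintervention evaluation among those its assessors cover, the Recruitment section does not say who takes the screening readings, and nothing says its 10-minute protocol is dropped later.
- **That the provider focus group unblinds the physicians.** It takes place after the month 9 follow-up and cannot affect any primary reading.
- **That research assistants are automatically safe substitutes.** They assess feasibility, and Table 1 includes fidelity items such as BP uploads at 3, 6 and 9 months. An assistant who sees upload data at month 3 could know the arm at months 6 and 9. Measuring BP before the questionnaires would not cure this.

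It is also fair to say that the 3 to 5 mmHg difference has no documentary basis, that the clinic device is not stated, and that sampling error in a pilot of this size exceeds the illustrated shift. The figures therefore show sensitivity, not expected bias. Sampling error is also reflected in the confidence interval, whereas a systematic difference in reading is not.

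**Conclusion.** The point holds in conditional form. As described, the primary outcome would be read by someone who knows the arm unless independent assessors are used, and the blinding statement cannot be true of the cluster physicians. This rests on cross-reading the Blinding, Trial design, Provider level and Follow-up phase sections with the abstract. The one inferred step is that the assessing physicians are the cluster physicians.

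The size is not known. Under the assumed SD of 18 mmHg and a differential reading of 3 to 5 mmHg, the shift in the proportion controlled is about 7 to 11 percentage points with the mean at 140, and about 4 to 8 points with the mean one SD away. The calculation uses the systolic criterion only. The contradiction does not depend on these figures.

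The trial is a feasibility pilot sized for precision, not power. Correction is still needed, because BP control is named as a primary outcome and its blinded assessment is asserted in both the abstract and the methods.

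**What to change.** Take the study BP at baseline, 3, 6 and 9 months with the 10-minute protocol already described under Recruitment, averaging the last two readings, and base the primary endpoint on those readings alone. The measurers should be already-planned study staff who are not any of the four cluster physicians, receive no PINGS reports, and neither complete nor see fidelity data (BP uploads, opening of messages) at any visit. State this in the Blinding section and align the abstract and the Follow-up phase section with it. If separate assessors already exist, naming them and confirming these conditions is enough.

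If this cannot be arranged, withdraw the physician blinding claim from the abstract and the Blinding section and report the primary outcome as assessed unblinded.

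The cost is protocol wording, some reallocation of research-assistant tasks so that BP measurement is kept apart from fidelity work, and a few minutes at visits already scheduled.
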